#### Awareness rate of cognitive impairment knowledge

By comparing the awareness rate of cognitive impairment knowledge before and after the intervention, the effect of education campaign will be evaluated. The contents will focus on basic cognitive impairment prevention knowledge.

### Sample size

PASS 15.0 software calculated the sample size. Power calculation indicated that with a sample size of 4 clusters in each group and 100 observed objects in each cluster, this study would have 88% power to detect the change in cognitive function with a mean of 1, a standard deviation of 2, and a two-tailed significance level of 5%. As a result of the correlation coefficients being set to 0.050 within clusters, and the coefficients of variation being set to 0.650, four clusters in each group, resulting in a total of 800 people to be recruited. The power of RCT over 80% is considered acceptable [41], so the sample size calculated in this study will be eligible.

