### Statistical methods

#### Primary and secondary outcomes

The primary purpose of the analysis was to investigate the effects of multicomponent interventions (targeted promotion campaigns, providing free cards and chess leisure activities tools) on objectively measured cognitive function and neuropsychiatric state, compared with the usual practice at 24-month follow-up.

The primary outcome analysis is powered to detect a significant difference in cognitive function and neuropsychiatric status in the older people over 60 years at the end of a 24-month follow-up period. Linear multilevel models will be used to analyze the cognitive function and other neuropsychiatric indicators as outcome variables. Levels indicate the clustering of residents within villages. We take the randomly divided classification variables as independent variables (the intervention group will be compared with the control group), and age, family history of dementia, baseline value, smoking, drinking, and sleep quality as confounding factors. In these linear multilevel models, village clusters will be included as a random effect to simulate the heterogeneity of residents in villages. The model will use restricted maximum likelihood estimation.

After the survey, the differences in baseline characteristics between participants who completed the whole survey and those who dropped out of the study will be compared. Multiple interpolation and sensitivity analyses of missing data are carried out to evaluate the influence of missing data on the obtained results. The effect size of the protocol will be determined by the subjects who participated in the study and completed follow-up. Secondary outcomes measured at other time points will be analyzed using similar methods. In addition, we will use repeated measurement variance analysis to evaluate the changes in the main outcome indicators of each protocol at each time point. Subgroup analyses are planned for baseline characteristics that might affect the primary outcomes.

The p values of all tests are two-sided and the test level α is 0.05. Estimates will also be reported with a 95% confidence interval.

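### The stated 88% power does not follow from the stated inputs: at two-sided 5% they give about 80%, and about 65% with a test that respects the 8 villages

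*Protocol article*

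**What the plan says.** The Sample size section of the protocol article prints a complete calculation. The design is "with a sample size of 4 clusters in each group and 100 observed objects in each cluster", and the claim is "this study would have 88% power to detect the change in cognitive function with a mean of 1, a standard deviation of 2", at "a two-tailed significance level of 5" percent. Clustering enters through "correlation coefficients being set to 0.050 within clusters, and the coefficients of variation being set to 0.650". The total is 800 people.

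The section then accepts this size on the ground that "The power of RCT over 80% is considered acceptable".

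Under Statistical methods (Primary and secondary outcomes), the analysis is a linear multilevel model with village as a random effect, fitted by restricted maximum likelihood, and "The p values of all tests are two-sided and the test level α is 0.05". Sequence generation confirms that 8 villages are randomized, stratified by county.

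**The concern.** Every input to the power calculation is printed, so the 88% can be checked without outside figures. It looked too high for two reasons. First, an intracluster correlation of 0.05 with 100 people per village inflates the variance about sixfold, which leaves roughly 63 to 67 effectively independent people per arm. Second, with only 8 randomized units, a normal or large-sample reference for the treatment contrast is too optimistic.

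This one figure supports the trial's size. If it is wrong, the chance of missing a true 1-point difference is not the implied 12%, and a non-significant result could be read as stronger evidence of no effect than the design can supply.

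**Working it through.** **Inputs** (all from Sample size): K = 4 villages per arm; m = 100 per village; difference 1; SD 2; ICC 0.05; CV 0.65, read as the CV of cluster size; two-sided α = 0.05. The sidedness is confirmed under Statistical methods.

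**Formulas.** SE = SD × √(2 × DE / (K × m)), where DE is the design effect. Normal power ≈ Φ(difference/SE − 1.96). For the small-sample version, power comes from the noncentral t distribution with 8 − 2 = 6 df (critical value 2.45) and noncentrality difference/SE.

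**Attempt to reproduce 88%**

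1. *Equal village sizes (CV ignored).* DE = 1 + 99 × 0.05 = 5.95. SE = 2 × √(2 × 5.95/400) = 0.345. Ratio 2.90. This is the most favourable reading, since unequal sizes can only lower power.
2. *CV 0.65, relative-efficiency correction.* λ = 5/(5 + 0.95) = 0.840. Relative efficiency = 1 − 0.4225 × 0.840 × 0.160 = 0.943. DE = 5.95/0.943 = 6.31. SE = 0.355. Ratio 2.82.
3. *CV 0.65, heavier design effect.* DE = 1 + ((1 + 0.4225) × 100 − 1) × 0.05 = 8.06. SE = 0.402. Ratio 2.49.

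| Variant | DE | Two-sided 5%, normal | Two-sided 5%, t on 6 df | One-sided 5%, normal |
|---|---|---|---|---|
| Equal sizes | 5.95 | 82.6% | 67.8% | 89.5% |
| CV 0.65, efficiency correction | 6.31 | **80.4%** | **65.3%** | **87.9%** |
| CV 0.65, heavier design effect | 8.06 | 70.2% | 55.1% | 80.1% |

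Replacing the normal by a t on 798 df changes the 80.4% only to 80.3%. With no clustering at all, power is essentially 100%. No two-sided variant tried gives 88%.

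**What would give 88%**

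- The same inputs with a one-sided 5% test: 87.9%.
- 5 villages per arm at two-sided 5%: ratio 1/(2 × √(2 × 6.31/500)) = 3.15, power about 88%.
- At two-sided 5% with 4 villages per arm: an ICC of about 0.038, or an SD of about 1.80.

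None of these is the stated design. The one-sided match suggests a software setting, but the settings are not shown, so that remains an inference.

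**Detectable difference.** With 6 df, 80% power needs a ratio of 3.37, so the detectable difference is 3.37 × 0.355 = 1.20 points.

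**Attrition.** The total of 800 is 8 × 100, with no allowance for loss. If 20% were lost (an assumption), leaving 80 per village, power would be about 78% (normal) or 63% (6 df).

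**The case against.** The strongest reply accepts that 88% is not reproduced but disputes the 65%. The protocol gives no degrees-of-freedom method, which an article may leave to the analysis plan, so 6 df is the reviewer's choice. Nor is it the only candidate. Villages are matched within county, and an analysis of four pairs would leave 3 df and 48.7% power at the same variance, although matching could reduce that variance. In the other direction, the model adjusts for the baseline value. If the SD of 2 is not already net of that adjustment and the baseline correlation were 0.5 (an assumption), power would be about 90% (normal) or 77% (6 df); at 0.6 it would reach 83% even with 6 df. Further, 0.650 is not labelled as the CV of cluster size, and 80.4% does still exceed 80%.

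Part of this stands. The 65% is conditional and should be labelled so, and the 80% has a range of about 70% to 83% according to how the CV is handled. But none of it restores the 88%. The document gives no baseline correlation and attaches the SD of 2 to the change in cognitive function, so baseline adjustment cannot justify a figure presented as following from the printed inputs. Ignoring the CV altogether still gives only 82.6%. And 80.4% clears the threshold only with a large-sample reference and complete follow-up over 24 months.

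**Conclusion.** The concern holds. At the stated two-sided 5% level, the stated inputs give about 80% power by normal approximation (80.4%), not 88%. This rests on reading 0.650 as the CV of cluster size with the usual efficiency correction.

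With a t reference on 6 df, the natural one for two arms and 8 randomized villages, power is about 65%. This assumes no further gain from covariates and no pairing in the analysis. The risk of missing a true 1-point difference is therefore about 20% or 35%, against the 12% implied. The claim of adequacy because power exceeds 80% is borderline on the first basis and not met on the second.

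Confidence is high that 88% is wrong as written. The 65% is sound but conditional on the assumptions named.

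**What to change.** Keep the 8 villages and correct the Sample size paragraph:

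- State that, for a 1-point difference with SD 2, ICC 0.05, CV of cluster size 0.65 and two-sided 5%, power is about 80% by normal approximation and about 65% with a t reference on 6 df. Give the detectable difference of about 1.2 points at 80% power (6 df).
- Report the software settings used, including sidedness and number of clusters, so that the figure can be reproduced. If the SD of 2 is meant before baseline adjustment, give the assumed baseline correlation and its source.
- Delete the sentence that calls the size adequate because power exceeds 80%.
- Name the scale to which the difference of 1 and SD of 2 refer, since both the MMSE and the MoCA are listed as primary measures of cognition.
- State that the calculation makes no allowance for loss to follow-up.

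The cost is one corrected paragraph in the protocol and the registry entry, and a less favourable power figure. No participants are added and the analysis model is unchanged.

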### Assignment of interventions: allocation

#### Sequence generation

In this cluster randomized controlled trial (RCT), 8 villages will be recruited. A village is a cluster. To reduce contamination risk, clusters will be randomized at the village level. Using a computer-generated list, statisticians at Ningxia Medical University randomly assigned villages (clusters) to one of the two groups and stratified them according to the counties to which villages belong before allocation. The randomization will be performed using a computer-generated randomization table in Microsoft Excel.

Randomization will be carried out after the cluster completes the baseline measurement. These clusters will be recruited from Helan County, Litong District, Qingtongxia City, and Shapotou District in Ningxia, China. Our goal is to recruit 800 over-60 s in 8 clusters. Clusters will be randomly assigned to accept one of the following conditions: (1) intervention groups that distribute leisure activities tools (chess and cards) free of charge and promote them, or (2) control groups (routine).

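### The power is computed for 800 people observed and recruitment is set at the same 800, so the printed figure allows for no loss over 24 months; the direct cost is modest, about 1.5 to 2 points of power at an assumed 20% loss

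*Protocol article*

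**What the plan says.** The Sample size section of the protocol article describes a calculation "with a sample size of 4 clusters in each group and 100 observed objects in each cluster" and reports that "this study would have 88% power to detect the change in cognitive function". The inputs are given as "with a mean of 1, a standard deviation of 2, and a two-tailed significance level of 5" per cent, with a within-cluster correlation of 0.050 and a coefficient of variation of 0.650. The recruitment figure follows directly: "four clusters in each group, resulting in a total of 800 people to be recruited". The section closes by accepting the size because power above 80% is considered acceptable.

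The section on sequence generation repeats the number: "Our goal is to recruit 800 over-60 s in 8 clusters". No retention or dropout rate is stated in the article.

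The primary comparison is at 24 months. The statistical methods (Primary and secondary outcomes) expect losses by then: "the differences in baseline characteristics between participants who completed the whole survey and those who dropped out of the study will be compared". They plan multiple imputation (worded as interpolation) and sensitivity analyses for missing data. The next sentence reads: "The effect size of the protocol will be determined by the subjects who participated in the study and completed follow-up".

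**The concern.** Power for a 24-month outcome depends on how many people have that outcome, not on how many were enrolled. Here the two numbers are the same: 8 × 100 = 800 enters the calculation and 800 is the recruitment target. That is consistent only if nobody is lost in two years, and the article's own analysis section does not expect that. The design guarantees no reserve either, because a village qualifies with as few as 100 residents of the target age, before exclusions and consent.

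What is at stake is the accuracy of the printed power and of the closing statement that the size satisfies the 80% criterion. Both refer to a sample that any loss makes smaller.

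**Working it through.** **Inputs** (Sample size section): K = 4 villages per arm, m = 100 per village, difference 1, SD 2, ICC 0.05, coefficient of variation 0.65 (read as that of cluster size), two-sided 5%. Assumed because the article gives no figure: loss of 5% to 30%, equal across villages.

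**Formulas**

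- Equal clusters: DE = 1 + (m − 1) × ICC.
- Unequal clusters (relative-efficiency correction): DE = [1 + (m − 1) × ICC] / [1 − CV² × L × (1 − L)], with L = m × ICC / [1 + (m − 1) × ICC].
- SE = 2 × √(2 × DE / (4m)); power = Φ(1/SE − 1.96).

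**Step 1: the plan's own figure at m = 100.**

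- Equal clusters: DE = 1 + 99 × 0.05 = 5.95; SE = 2 × √(11.90/400) = 0.345; power = Φ(2.899 − 1.96) = 82.6%.
- CV 0.65: L = 5/5.95 = 0.840; DE = 5.95 / (1 − 0.4225 × 0.840 × 0.160) = 6.31; SE = 0.355; power = Φ(2.815 − 1.96) = 80.4%.

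Neither is 88%. With CV 0.65 and a one-sided 5% test, power = Φ(2.815 − 1.645) = 87.9%, which matches the printed figure but not the stated two-tailed level.

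**Step 2: power as the number observed per village falls.** The first column takes 88% at face value: 1/SE is set to 1.960 + 1.175 = 3.135 at m = 100 and scaled by the ratio of SEs under CV 0.65. The other two use the stated inputs directly, two-sided.

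| Observed per village | Assumed loss | From 88% | CV 0.65 | Equal clusters |
|---|---|---|---|---|
| 100 | 0% | 88.0% | 80.4% | 82.6% |
| 95 | 5% | 87.7% | 79.98% | 82.3% |
| 90 | 10% | 87.3% | 79.5% | 82.0% |
| 80 | 20% | 86.4% | 78.5% | 81.1% |
| 70 | 30% | 85.3% | 77.1% | 80.1% |
| 50 | 50% | 81.8% | 73.1% | 76.8% |

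The cost at 20% loss is 88.0 − 86.4 = 1.6, 80.4 − 78.5 = 1.9 and 82.6 − 81.1 = 1.5 points. At 30% it is 2.7, 3.3 and 2.5 points.

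**Step 3: why the cost is small.** With unlimited people per village the SE would still be 2 × √(2 × 0.05/4) = 0.316, against 0.345 to 0.355 at 100 per village. Most of the variance comes from having four villages per arm, so losing people within villages changes little.

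**Step 4: where 80% is crossed.** From 88% at face value, power is 81.8% at 50 per village and 78.9% at 40, so more than half of each village would have to be lost. From 80.4%, at least 96 per village are needed, so a 5% loss crosses the line. With equal clusters, 70 per village still gives 80.1%, so the line is reached at about 30% loss.

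**The case against.** The strongest reply is that the article claims 88% against a criterion of 80%, an 8-point margin that ordinary dropout does not use up. On the printed figure that is right: 20% loss leaves 86.4%. A reader might infer from the recomputed 80.4% that there is almost no margin and that 5% loss makes the trial miss its own criterion. The document does not support that as an effect of dropout. It arises only after 88% has been replaced because it fails to reproduce, which is a different problem. It also rests on 79.98% against 80% in one variant. Ignoring unequal cluster size keeps power above 80% down to 70 per village, and a t reference with 6 degrees of freedom for eight villages gives about 65% (CV 0.65) to 68% (equal clusters) before anyone is lost.

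Two points of wording also count. The observed objects of the Sample size section may simply mean study subjects, since the Study setting section uses similar language for enrolment. And the completer sentence is loosely phrased and stands beside planned multiple imputation, so completers may not be the only analysis set. Both soften any charge of outright contradiction. Neither supplies a retention allowance: on either reading the calculation uses 100 outcomes per village, and imputation does not restore the information in outcomes that were never measured.

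**Conclusion.** The point stands as a modest flaw in a stated figure. The multiplication 8 × 100 = 800 is correct; the fault is that one number serves as both the recruited and the analysed sample, while the analysis section expects dropouts. The printed power is overstated on this account by about 1.5 to 2 points at 20% loss and about 3 points at 30%. This assumes equal loss across villages, the coefficient of variation read as that of cluster size, and loss rates that are not in the document.

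Whether the 80% criterion is missed cannot be settled from dropout alone. It depends on which starting power is right, and so on resolving why 88% does not reproduce at the stated two-tailed 5%.

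A reader might also suppose that people who leave gain nothing and so dilute the difference (to 0.8 at 20% loss), with a much larger fall in power. The document plans no imputation of that kind, and an effect estimated in completers would not be diluted in that way, so that reading is not supported.

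**What to change.** In the Sample size section, separate the number recruited (800, 100 per village) from the number expected to be observed at 24 months under a stated retention assumption. Recompute power at that second number with the stated two-sided 5%, ICC and coefficient of variation, and print the result in place of the present figure. Keep the statement that the size meets the 80% criterion only if the recomputed power does.

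The cost is one recalculation, a few words, and a slightly less favourable stated power. No additional participants are required.

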### Assignment of interventions: allocation

#### Sequence generation

In this cluster randomized controlled trial (RCT), 8 villages will be recruited. A village is a cluster. To reduce contamination risk, clusters will be randomized at the village level. Using a computer-generated list, statisticians at Ningxia Medical University randomly assigned villages (clusters) to one of the two groups and stratified them according to the counties to which villages belong before allocation. The randomization will be performed using a computer-generated randomization table in Microsoft Excel.

Randomization will be carried out after the cluster completes the baseline measurement. These clusters will be recruited from Helan County, Litong District, Qingtongxia City, and Shapotou District in Ningxia, China. Our goal is to recruit 800 over-60 s in 8 clusters. Clusters will be randomly assigned to accept one of the following conditions: (1) intervention groups that distribute leisure activities tools (chess and cards) free of charge and promote them, or (2) control groups (routine).

### Allocation concealment and blinding

Given the nature of the study, participants can't turn a blind eye to the interventions they receive. The researchers collecting data and managing participants are blinded to the groups and will not know the groups until the data analysis is complete.

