### Outcomes

Uniformly trained researchers will evaluate results at three time points: baseline, 12 months, and 24 months following baseline. During the baseline survey, researchers will fully explain the purpose and content of the study to the participants. If participants are willing to join the study, they will sign a written informed consent. Measurements will only be made after informed consent is given. Cognitive function, depression, anxiety and loneliness, frequency of leisure activities, demographics, and awareness rate of cognitive impairment will be measured. The schedule of enrolment, interventions, and assessments is outlined in Fig. 1.

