### Primary outcomes

#### Cognitive function

The Mini-Mental State Examination (MMSE) [34, 35] and Montreal Cognitive Assessment (MoCA) [36] are simple, low cost and noninvasive methods of screening MCI due to Alzheimer’s disease (AD). Numerous studies stated that MMSE and MoCA accuracy in detecting MCI due to AD was inconsistent when selecting different reference standards as the “gold standard. In addition, they selected different cutoff values for positivity. To date, there is still no consensus on which neuropsychological test performs better at detecting MCI due to AD. In addition, international criteria are more suitable as a reference standard for evaluating diagnostic tools' accuracy. Studies have shown that the combined use of MMSE and MoCA scales for cognitive impairment diagnosis is more accurate than MMSE or MoCA scales alone. Therefore, we use MMSE and MoCA together to assess cognitive function. The ability to perform activities of daily living (ADL) is a vital part of the assessment in neurologic patients. An ADL scale was used to evaluate subjects' functional status in real life. It consists of two parts: the Physical Self-Maintenance Scale (PSMS) and Instrumental Activities of Daily Living (IADL).

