### Data collection and management

Research assistants blinded to the allocation will be trained in data collection. Participants will be observed and surveyed using questionnaires throughout the study period. The medium-term and long-term effects of the intervention were evaluated by repeated measurements using the same standardized procedures before, 12 months, and 24 months after the intervention.

All collected data will be kept strictly confidential and properly preserved, and all relevant regulations will be observed. Each participant is identified by a unique code instead of a name. All research data can only be obtained by designated research team members before analysis. These data were initially registered on paper questionnaires by investigators and then entered into electronic data through Epidata 3.1 software after the investigation. Electronic data is stored on password-protected computers, and paper questionnaires are stored in locked filing cabinets. When collecting data, the project manager will check all data for omissions or errors and record any problems with the data. Before analyzing the data, the lead researcher (PI) and statistician will review it again. Information collected from the study will be preserved until the project is completed. From the date when the study results are published, they will be preserved for at least 5 years.

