### Process evaluation

A combination of questionnaires, interviews, and field observations will be used to assess the process. The purpose of process assessment is to understand: participants' different experiences of intervention measures; any differences between expected and observed results; sustainability of intervention programs; possible contamination between the intervention group and the control group; and any unexpected events in the process that are not part of the results of the study.

Attendance at communication campaigns will be recorded. Each cluster will have a special person to check intervention measures implementation. All activity processes will be recorded. In case of important modifications, they will be explained to the experimental participants in accordance with relevant regulations and agreed, and the modifications will be made in the trial registration center at the same time. After each follow-up, the project researchers will analyze the data and report the results to the PI. During the experiment, when force majeure fails to continue intervention or other situations must be terminated, the PI will make the final decision to terminate the trial.

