## Discussion

With the increase in age, the probability of cognitive impairment in the older people is on the rise [42, 43]. More and more evidence shows that participating in cards and chess leisure activities is beneficial to the cognitive and psychiatric state of the older people [18, 19]. Although previous cross-sectional or cohort studies have shown beneficial prospects for leisure activities [44, 45], the quality of the study design is low. Many previous studies have not fully considered baseline cognitive state and other confounding factors, both of which may lead to bias, and no effective cluster randomized controlled trials are underway. Advantages of this study include robust randomized controlled trial design, randomization at the cluster level to reduce contamination, large population, including medium-term and long-term follow-up measures, and strict objective scale measurement as the main results. In addition, the uniqueness of this study is that it will clarify the influence of the frequency and duration of participation in chess and cards activities on cognitive function. Inevitable limitations of this study include: First, due to the nature of this study, participants cannot turn a blind eye to the interventions they receive, and if researchers interact with subjects, they cannot keep blind to researchers, which may lead to information bias. Second, basic information, the duration and frequency of leisure activities are reported by the subjects themselves, which may lead to recall bias. Nevertheless, the present study will fill gaps in the literature. This study will help to build an evidence base around the effectiveness of interventions to reduce cognitive impairment in the older people, and provide valuable information for successful aging.

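### Assessor blinding is stated as a fact in the methods but conceded as unattainable in the Discussion, so for the follow-up MMSE and MoCA it is attempted, not assured

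*Protocol article*

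**What the plan says.** Two methods sections of the Protocol article claim blinding without qualification. Allocation concealment and blinding says of the researchers who collect data and manage participants that they "are blinded to the groups and will not know the groups until the data analysis is complete". The section on Data collection and management adds: "Research assistants blinded to the allocation will be trained in data collection".

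The Discussion, listing limitations that it calls inevitable, says otherwise: "if researchers interact with subjects, they cannot keep blind to researchers, which may lead to information bias".

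The contact in question is the outcome assessment. Under Outcomes: "Uniformly trained researchers will evaluate results at three time points: baseline, 12 months, and 24 months following baseline". Under Cognitive function, within the primary outcomes: "Therefore, we use MMSE and MoCA together to assess cognitive function".

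Process evaluation provides for analysis during the trial: "After each follow-up, the project researchers will analyze the data and report the results to the PI". Study setting calls the trial open-label.

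**The concern.** The methods assert a safeguard for the primary outcome, and the Discussion says that it fails once researchers and participants meet. A later report could quote the methods and claim blinded assessment that the same article disowns.

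The setting makes unmasking plausible. Allocation is by whole village, with eight villages of about 100 participants each, so one cue can unmask a whole cluster. MMSE and MoCA involve an examiner. An examiner who knows the arm may prompt or score differently, and that difference would enter the between-arm comparison at 12 and 24 months. Randomization follows the baseline measurement (Sequence generation), so baseline scores are safe. For the same reason, adjusting for baseline cannot remove a bias that arises later.

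**Working it through.** **1. The blinding statements side by side**

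- Allocation concealment and blinding: data collectors and participant managers are blind until analysis is complete. No condition is attached.
- Data collection and management: the research assistants who collect data are blind. No condition is attached.
- Discussion: blinding cannot be kept if researchers interact with subjects.

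The Discussion statement is conditional, so the question is whether its condition is met. Trained researchers evaluate outcomes at each time point, and managing participants is itself interaction. The condition is met whenever a researcher administers MMSE or MoCA.

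**2. Routes by which the arm could become known**

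- Each intervention participant receives game sets. The village has monthly lectures, social-platform content and an appointed motivator (Intervention group).
- Participants know their arm (Allocation concealment and blinding).
- The survey asks how often and for how long participants play chess and cards (Self-reported chess and cards leisure activities).
- Researchers visit the sites regularly (Patient and public involvement), and process evaluation uses interviews and field observation. The article does not say whether these staff are separate from the outcome assessors.

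**3. The 12-month analysis**

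The primary objective is at 24 months, and Process evaluation has an analysis and a report to the PI after each follow-up. The text does not say whether the report is by arm, or whether analysts and assessors overlap. The phrase about blinding lasting until analysis is complete also does not say which analysis is meant, the 12-month or the 24-month one.

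**4. Illustration of consequence**

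Inputs from Sample size: 4 clusters per arm (k), 100 per cluster (m), difference 1, SD 2, ICC 0.050, coefficient of variation (CV) 0.650, two-sided 5%, stated power 88%.

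- L = m·ICC / (m·ICC + 1 − ICC) = 5 / 5.95 = 0.840
- Design effect = (1 + 99 × 0.05) / (1 − 0.65² × 0.840 × 0.160) = 5.95 / 0.943 = 6.31
- SE = 2 × √(2 × 6.31 / 400) = 0.355

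The plan's own figure: this SE gives two-sided power of 80.4% (normal) or 65.3% (t, 6 df), not 88%. A one-sided 5% test gives 87.9%, but the article states a two-tailed one. That mismatch is a separate matter and neither supports nor weakens this point.

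Now suppose that there is no true effect and that the arms differ only by a scoring shift b. With the normal reference, the rejection probability is Φ(b/SE − 1.96) + Φ(−b/SE − 1.96).

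- b = 0.1: b/SE = 0.28, giving 0.0466 + 0.0125 = 5.9%
- b = 0.25: b/SE = 0.70, giving 0.1045 + 0.0039 = 10.8%

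| SE basis | SE | b = 0.1 (normal / t, 6 df) | b = 0.25 (normal / t, 6 df) |
|---|---|---|---|
| No CV adjustment (design effect 5.95) | 0.345 | 6.0% / 5.7% | 11.2% / 9.4% |
| CV adjustment as above (6.31) | 0.355 | 5.9% / 5.7% | 10.8% / 9.2% |
| Larger CV inflation (8.06) | 0.402 | 5.7% / 5.5% | 9.5% / 8.3% |

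The values of b are assumptions. The documents give none.

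**The case against.** The protocol does not hide the risk. It calls the trial open-label and names information bias as a limitation. Assessors are uniformly trained, procedures are standardized, and randomization follows baseline. All of this stands, and it is why the remedy is a reconciliation plus small safeguards and not a redesign. It does not remove the conflict, because the methods still assert unconditionally what the Discussion withdraws.

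Three stronger readings are tempting but not supported.

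- A reader might infer that 12-month reporting contradicts the blinding claim. Process evaluation does not say that the report is by arm or that assessors see it. Effects at 12 months are a stated secondary objective, so an analysis at that point is legitimate. What remains is an open question, not a proven contradiction.
- A reader might infer that the questionnaires disclose the arm. Both arms get the same measurements at the same times, and control participants keep their usual hobbies, which may include cards. Of the awareness items the article says: "The contents will focus on basic cognitive impairment prevention knowledge". That does not tie them to the lectures. The answers can hint at the arm, but they do not reveal it.
- A reader might take the false-positive figures as evidence of actual bias. They rest on an assumed shift, on an SE derived here from the sample size inputs and not stated in the article, and on no allowance for the planned baseline adjustment. With eight clusters the t reference, which gives the lower figures, deserves at least equal weight.

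It is also fair to say that the order of tests within a visit is not given in the text and that the assessment schedule figure is not shown. The proposed order is therefore a safeguard, not the correction of a known fault. Examiner scoring of MMSE and MoCA is likewise inferred from the nature of the tests and the Outcomes section. The Discussion describes the scales as strict and objective.

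**Conclusion.** The concern holds in a limited form. The blinding claimed in Allocation concealment and blinding and in Data collection and management conflicts with the Discussion, and the Discussion's condition is met at every cognitive assessment. Blinding of the 12- and 24-month MMSE and MoCA should be regarded as attempted, not assured. The 12-month analysis adds an unresolved route by which results by arm might reach assessors before the primary assessment. The documents do not show that it does.

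The size of any bias is unknown. With SE about 0.355, an assumed shift of 0.1 to 0.25 points (10% to 25% of the 1-point target) gives a false-positive rate of about 6% to 11% (normal) or 6% to 9% (t, 6 df) against 5%. These figures are illustrative only. The conflict in the text does not depend on them.

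**What to change.** - Reconcile Allocation concealment and blinding, Data collection and management, and the Discussion. State which roles are masked, and say that masking of outcome assessors is attempted and not assured. The open-label label in Study setting can stay.
- At each follow-up, administer MMSE and MoCA before the activity and awareness questionnaires.
- Have the assessor record a guess of the arm straight after the cognitive tests, so that the success of masking can be reported.
- Withhold 12-month results by arm from outcome assessors until the 24-month data are locked, and say so in Process evaluation.

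The cost is a fixed questionnaire order, one extra item and later circulation of the 12-month results by arm. No added staff are needed.
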